##### Module 3 Exercise

In Module 3, which talks about behavior activation, there is an exercise in which a participant can practice planning behaviors that make him/her feel better, following the basic principle of the behavioral activation treatment . First, he/she is asked to type in a box on the screen behaviors that might make him/her feel better. A total of 128 popular behaviors that might make people feel better (eg, walking and listening to music) were collected from 12 clinical psychologists, with ratings of the degree of being easily executed and the possible effect on mood for each behavior. A total of 33 behaviors not recommended for behavioral activation (eg, drinking alcohol to excess, gambling, etc) were also collected. The aforementioned large online survey asked the 2800 respondents to rate whether each of the 128 behaviors would make them feel better. A total of 40 behaviors that were endorsed by 1% or more of the respondents for men or women were selected to be part of the recommended list, because of the high diversity of the responses. These behaviors were sorted by a sum of the ratings of the degree of being easily executed and the possible effect on mood by clinical psychologists.

The list is used to help a participant to list behaviors that might make him/her feel better in the first part of the exercise, taking into account the sex of the participant. Participants will be asked to select up to three behaviors that they would like to try. Each of these behaviors will be evaluated by using an algorithm to be recommended or discouraged. This algorithm compares an input word or phrase with words or phrases in the list of recommended behaviors or that of nonrecommended behaviors. If it matches, the algorithm will show a label of being “recommended” or “avoided” for that behavior [43]. In the latter case, a message will appear to suggest reconsidering engaging in that behavior. In the next step, participants will be asked to rate each behavior on the degree of ease of execution and its expected effect on their mood using a scale from 0 to 10, and then, the system will recommend the behavior with the highest sum scores the most. Based on their preferences and the recommendation from the system, participants will select one behavior to set up a behavior activation plan, such as the date and place to execute the behavior. They will be able to save the plan to the system, and come back to review it later. An additional option function will follow-up the adherence of participants to the plan. Following the date set up to carry out the plan, the system will ask participants if they have finished the plan and how their moods have been changed by it. Based on their responses, the system will provide the participants with automatically generated comments and advise them to continue the plan or change to another one.

##### Module 4 Exercise

In Module 4, which discusses cognitive restructuring (part 1) and awareness of the association between thoughts and moods, an exercise will help participants become aware of how their thoughts and moods are associated. This exercise starts with 10 questions on schemas that may underlie maladaptive ways of thinking (such as black or white thinking, overgeneralization, etc) [22]. Participants will be asked whether these schemas apply to their own thinking. The data will be stored in the system for later use. Like the second exercise of Module 2, in this exercise, participants will be asked to enter a stressful event or situation, thoughts, and moods (three of the five components of the CBT model) into corresponding boxes on the screen; they will be permitted to do this exercise either based on their own experience or by selecting one of five fictitious cases provided by the system, or using previous saved data that they created in the second exercise of Module 2. They will also be asked to rate the extent to which they feel each presented mood on a scale from 0 to 100. The responses in the three boxes will be automatically scored by an algorithm developed by the authors to assess its accuracy, with each one being scored 0% to 100%, and categorized into four quartile groups using the sample data as a norm. Participants will be encouraged to redo the input if their score is not in the top 25%. In the next step, they will be asked to select the most relevant thought and mood if there are multiple ones. In the final step, they will be asked to think about whether the selected thought and mood are associated, in other words, if the mood would change if the thought changes. If the participants confirm the association, the exercise ends. If not, the participants will be asked to go back to the selection of thoughts and moods and redo the exercise.

##### Module 5 Exercise

In Module 5, which discusses cognitive restructuring (part 2), that is, changing mood through balanced thinking, an exercise to cover all the steps of cognitive restructuring will be presented. Participants will be asked to (1) fill in events, thoughts, and moods; (2) select one thought that is most relevant to the mood; (3) review the association between the thought and mood; (4) describe evidence that supports the thought; (5) search for evidence that does not support the thought; and (6) engage in balanced thinking and monitor changes in mood. Steps 1 to 3 use the same components of the Module 4 exercise. In step 4, participants will be asked to enter reasons that they think the thought is true (ie, evidence that supports the thought), and indicate their degree of confidence for the reason. Then, they will be asked to enter evidence that does not support the thought, which is sometimes a hard step for people.

A system was developed to help participants be aware of evidence that does not support their thoughts in three ways. First, refer to a list of 12 patterns of evidence that does not support the thought, which was developed through extensive discussion by a group consisting of clinical psychologists, mental health researchers, and master’s and doctoral students specializing in mental health, to classify patterns of 289 sets of evidence that does not support the thought extracted from data already collected from the five-part CBT case formulation reported by participants in a previous iCBT program [18]. Second, considering that the use of old sayings may help in communicating therapeutic techniques with patients and bringing about cognitive reframing in CBT [44,45], refer to a selection of 50 well-known sayings rank-ordered by the frequency of endorsement for possible effects on improving mood or reducing stress calculated from data collected via an internet survey of full-time employees (N=4120), expecting that participants may find a new way of thinking beyond their schemas by studying the philosophy underlying the saying. Third, for schemes reported by participants in the Module 4 exercise, common tips to find evidence that does not support the thought are suggested by the system, which were developed through a discussion among clinical psychologists and mental health researchers. Once words or phrases of evidence that does not support the thought are entered, the participant is asked to rate the degree of confidence for each word or phrase, using a scale from 0 to 100.

The next screen shows all the information entered about the event, the thought, the list of moods, the evidence that supports the thought, and the evidence that does not support the thought. Then, the participants will be asked to create statements that reflect balanced thinking. Tips to help participants to create balanced thinking will be provided if they request them. They will also be able to ask the system to show a sample statement of balanced thinking, which will be created by automatically connecting a word/phrase of evidence that supports the thought and a word/phrase for evidence that does not support the thought, with the highest confidence rating.

In the final step of the exercise, after participants have created the statement of balanced thinking, they will be asked to rate their mood using a scale from 0 to 100. The system automatically detects changes in mood from those entered in the mood box before, and shows an “improvement” message when mood improves. Finally, participants will be asked to rate their overall mood change using a 4-point scale (a lot, to some extent, not much, and not at all). If they rate their mood change as a lot or to some extent, the exercise will end, with a suggestion to keep the statement of balanced thinking and use it in their daily life; otherwise, they will be encouraged to try again with other evidence that does not support the thought or with an alternative statement of balanced thinking.

### Intervention Group

Participants in the intervention group will be invited to access and study the SMART-CBT program for 10 weeks in total (ie, a 6-week main study period followed by a 4-week review period) after the baseline survey. Participants in the intervention study may quit participating in or continuing the intervention solely based on their decision. During the first 6 weeks, the intervention group will be notified every Monday via email that a new module is available for the study. When participants do not complete a module by that Friday, they will receive an email reminder to encourage them to complete the module. After the initial 6 weeks, those who complete all six modules (except for the COVID-19 module) will receive a weekly email to encourage them to review the modules. If participants do not complete any module (other than the COVID-19 module), they will receive an email reminder to encourage them to review the modules. Ten weeks after the baseline survey, the intervention program will be closed.

### Control Group

Participants in the control group will not receive any intervention program during the study period. Participants in both the intervention group and the control group will be able to use an internal occupational health service and/or employee assistance program service, depending on the policy of their workplace. Participants in the control group will be provided a chance to use the intervention program after the study period.

### Outcomes

All outcomes will be measured by using online questionnaires. Nonrespondents will receive a reminder email from the research center to participate in the surveys. Outcome measures other than the occurrence of an MDE will be assessed at baseline and at two follow-up time points, 3 and 6 months after the baseline survey. MDEs will be assessed at baseline, and 6- and 12-month follow-ups. Table 2 provides an overview of the outcome measures for each survey.

**Table 2 table2:** Outcomes to be evaluate in this study: measures and timing of measurement.

Outcome		Measure	Baseline (T1)	3-month follow-up (T2)	6-month follow-up (T3)	12-month follow-up (T4)
**Primary outcome**						
	Depression	BDI-II^a^	Yes	Yes	Yes	No
**Secondary outcomes**						
	Psychological distress	K6^b^	Yes	Yes	Yes	No
	COVID-19 fear	Fear of COVID-19 Scale	Yes	Yes	Yes	No
	The total number of sickness absence days in the past 3 months	An original item	Yes	Yes	Yes	No
	Major depressive episodes^c^	MINI^d^ depression section: self-report	Yes	No	Yes	Yes

^a^BDI-II: Beck Depression Inventory II.

^b^K6: Kessler psychological distress scale.

^c^While major depressive episodes will be measured at 6- and 12-month follow-ups, the information will be combined to create a variable for major depressive episodes during the 12-month follow-up.

^d^MINI: Mini-International Neuropsychiatric Interview.

#### Primary Outcomes

The primary outcomes of the study are depression and psychological distress at 3- and 6-month follow-ups. Depression will be measured with the Japanese version of Beck Depression Inventory II (BDI-II) [46,47], a 21-item self-report inventory of depressive symptoms in the past 2 weeks, with each item to be scored from 0 to 3. The total scale score will be calculated and used as a measure of the severity of depressive symptoms.

#### Secondary Outcomes

The secondary outcomes include psychological distress, fear of COVID-19, sickness absence days at 3- and 6-month follow-ups, and MDEs at the 12-month follow-up. Psychological distress will be measured with the Japanese version of Kessler’s psychological distress scale (K6) [48,49], a six-item scale of psychological distress (depression and anxiety) in the past 30 days, with a response option range from 0 (none of the time) to 4 (all of the time). The total scale score will be used as an indicator of the degree of psychological distress. Fear of COVID-19 will be measured with the Japanese version of the Fear of COVID-19 Scale (FCV-19S) [50,51], which is a seven-item scale to measure fear reactions to the COVID-19 infection. Each item is rated on a 5-point scale (1-5), and the total score (7-35) will be used as the measure of the degree of fear of COVID-19. Sickness absence days in the past 3 months will be measured using the following single-item question [37]: “How many days did you miss an entire work day because of problems with your health during the past 3 months? (please include only days missed for issues with your own health, not someone else’s health.).” The presence of a MDE will be measured with a self-report scale developed based on the MINI [52] according to the Diagnostic and Statistical Manual of Mental Disorders-5 criteria [53]. The same set of nine questions from the MDE section of the MINI will be used to assess whether a participant has had a MDE in the past 12 months, followed by questions on the onset and the most recent time the participant has had symptoms of a MDE in the past 12 months. The sensitivity and specificity of this instrument for the clinical diagnosis of major depression were reported as 0.86 and 0.67, respectively, in a sample of psychiatric outpatients (n=31) in a pilot study. The self-report MINI for MDEs will be measured at 6- and 12-month follow-ups, as well as at baseline. Combining participants’ responses to these two follow-up surveys, any MDE reported after baseline and the timing of onset (number of months since baseline) will be used as the MDE outcome during the 12-month follow-up period.

### Process Evaluation

Information on the usage of the intervention program by participants in the intervention group will be collected from the records of the program. Questions will be asked in the baseline and follow-up questionnaires to gather information about respondents’ self-reported knowledge and self-efficacy regarding stress management in general, as well as the CBT components of the program (cognitive restructuring, behavioral activation, assertive communication, problem solving, and relaxation training) as follows: for knowledge, “how much knowledge do you have about…” and for self-efficacy, “how confident are you that you can do….,” with a 5-point scale ranging from 0 (none) to 4 (enough) [18].

### Implementation Outcomes

Implementation outcomes will be measured with the user version of the Implementation Outcome Scales for Digital Mental Health (iOSDMH) (unpublished study "Implementation Outcome Scales for Digital Mental Health (iOSDMH): a scale development and cross-sectional study" by [name] et al, 2021), a 19-item scale, with a 4-point Likert-type response option, as follows: three items for acceptability, four items for appropriateness, six items for feasibility, five items for harms, and one item for overall satisfaction. Participants in the intervention group will be asked to complete the questionnaire online at the 3-month follow-up. Participants in the intervention group will also be asked additional questions regarding the reasons for not participating in the program or discontinuing the program if they do so.

### Demographic and Other Characteristics

Demographic data, such as sex, age, education, marital status, occupation, type of employment contract, type of work shift, frequency of remote work (working from home), treatment of chronic physical conditions and mental disorders, and overtime hours during the past month, will be collected.

### Sample Size Calculation

The required sample size was calculated for one of the outcome variables, ie, depressive symptoms assessed by BDI-II. Previous meta-analyses of web-based universal prevention psychological interventions for improving depression and anxiety in the workplace yielded a summary effect size of 0.25 [8]; our previous study of a guided universal prevention iCBT program among workers reported a smaller effect size on depression (*d*=0.16) at a 6-month follow-up [18]. To detect a minimal effect size of 0.15 at an alpha of .05 and a power of 0.80, the estimated sample size is 699 participants in each group. The statistical power was calculated using the G*Power 3 program [54].

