## Methods

### Trial Design

The study will be a nonblinded, parallel, two-arm RCT with a single intervention group that will receive the SMART-CBT intervention and a control group that will receive TAU. The allocation ratio of the intervention group to the control group is 1 to 1. Participants will be randomly allocated to either the intervention group or the control group after they have completed a baseline online questionnaire. Follow-up surveys will be conducted at 3, 6, and 12 months after the baseline measurement, using online questionnaires. The study protocol has been registered at the UMIN Clinical Trials Registry (UMIN-CTR; ID UMIN000043897). This protocol manuscript has been reported according to the SPIRIT (Standard Protocol Items: Recommendations for Interventional Trials) guideline checklist [19].

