### Procedure

Participants will be recruited from a pool of 300,000 people living in all 47 prefectures of Japan who registered with an online survey company. A clinical research coordinator (CRC) from the survey company will send an invitation to this population, with a description of the study’s aim and procedure, and obtain online informed consent to participate in the study. We will recruit 1600 participants in total, including 200 males and 200 females in each of four age groups (20-29, 30-39, 40-49, and 50-60 years old). The CRC will ask those who agree to participate in the study to complete an online questionnaire for the baseline survey. We expect that at least 1400 individuals will be eligible based on the inclusion and exclusion criteria. These participants will be randomly allocated to either the intervention group (n=700) or the control group (n=700). Participants in the intervention group will be asked to use the intervention program for 6 weeks after the baseline survey, and they will be encouraged to revisit and review the program for an additional 4 weeks. Participants in the control group will be given a chance to receive the intervention program upon completion of the study. The participants in the intervention group will be given a token equivalent to JPY 1000 (USD 9.1) if they complete all modules of the program. The participants in the control group will be given a token equivalent to JPY 100 (USD 0.91). Participants in both groups will be given a token equivalent to JPY 30 (USD 0.27) for completing each of the surveys (baseline, and 3-, 6-, and 12-month follow-up surveys).

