Job stressors and emotional reactions have been associated with poor levels of health [32] and work performance [33]. Job stressors may also have a spillover effect on family relationships [34] and a crossover effect on the well-being of a family member [35]. Informing participants of predictions regarding these possible outcomes of one’s work and life based on the self-assessment may motivate participants to engage in the program or even reduce depression [36]. Data from a large 1-year follow-up online survey (n=2800, with a response rate of 68%) of full-time employees conducted between 2018 and 2019 was used to develop a prediction model based on the above six scales at baseline for achievement at work and personal life-related outcomes. The former was measured on a presenteeism item from the WHO Health and Work Performance Questionnaire (range 0-10) [37,38], an item simply asking about any successful event in the job (yes=1 or no=0), and an item asking whether there had been any troublesome events at work (yes=1 or no=0). Personal life–related outcome measures included items regarding subjective health status (excellent/good=1 or fair/poor=0), trouble in family relationships (yes=1 or no=0), poor relationship with family (yes=1 or no=0), and any undesirable event for a family member (yes=1 or no=0). The model was developed using linear or logistic regression to predict these outcomes at follow-up on the six scale scores, adjusting for sex and age at baseline. A sum of regression coefficients for the six scales that were statistically significant was used as an index to indicate work performance or the probability of each event 1 year later and was expressed on a 10-point scale. A personalized message will be displayed on the screen with these predictions to inform the participant what could happen in his/her work and personal life in the next year, based on the current levels of job stressors and emotional reactions.

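### The 80% power claim assumes outcome data from virtually everyone randomised and a t-test rather than the planned group × time model, so it is unsupported as stated

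*Protocol article*

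**What the plan says.** All references are to the protocol article.

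- **Sample Size Calculation.** The target is set by "To detect a minimal effect size of 0.15"; for an alpha of .05, the section then gives "a power of 0.80, the estimated sample size is 699 participants in each group". The tool is named ("The statistical power was calculated using the G*Power 3 program"), but the test and its sidedness are not. There is no term for loss to follow-up and none for within-person correlation.
- **Trial Design.** "The allocation ratio of the intervention group to the control group is 1 to 1".
- **Procedure.** Eligible participants will be "randomly allocated to either the intervention group (n=700) or the control group (n=700"). The 1600 recruited are expected to yield at least 1400 who pass the eligibility criteria. That step is taken before randomisation.
- **Outcomes.** Follow-up is by online questionnaire, with reminder emails to people who do not respond.
- **Statistical Methods, Effectiveness of the Intervention.** The primary test is the group × time interaction at 3 and 6 months in a mixed model for repeated measures, by intention to treat. Missing values are handled by restricted maximum likelihood (REML) under missing at random. Cohen d is calculated only in those who complete the baseline and follow-up surveys.

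**The concern.** The number needed and the number randomised agree only if almost nobody is lost by 6 months. The surplus of 200 recruits is used up by ineligibility, so it gives no protection against loss. Elsewhere the article plans for nonresponse.

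The power figure also belongs to a different test. A two-group comparison of follow-up means does not involve the correlation between baseline and follow-up, whereas a group × time contrast depends on it strongly.

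There is little slack. The Objectives section hypothesises an effect of 0.16 to 0.25, and the authors' own earlier guided trial, cited in the sample-size paragraph, found 0.16. A modest loss moves the t-test's detectable effect up to or past that lower value. A reader who takes the 0.80 at face value would give a null result more weight against an effect of 0.15 than the stated calculation can bear.

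**Working it through.** **Inputs from the article:** d = 0.15 (SD taken as 1), alpha .05, power 0.80, allocation 1:1, 700 randomised per group. **Assumed, because the article does not give them:** loss by 6 months, correlation ρ between baseline and 6-month BDI-II, equal SDs at both times, and a two-sided test.

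**Step 1: reproduce the stated figure.** For a two-sample comparison, n per group = 2(1.960 + 0.842)²/0.15² ≈ 698 by the normal approximation. The noncentral t gives 698.6, hence 699. A one-sided test would need only 550, so the calculation was two-sided. Power at 699 is 0.8002 and at 700 is 0.8008. So 699 is correct as the number per group with outcome data.

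**Step 2: apply loss on the protocol's own basis.** Same t-test, with n = 700 × (1 − loss):

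| Loss | n per group | Power at d = 0.15 | d detectable with 80% power |
|---|---|---|---|
| 0% | 700 | 0.801 | 0.150 |
| 5% | 665 | 0.780 | 0.154 |
| 10% | 630 | 0.758 | 0.158 |
| 20% | 560 | 0.708 | 0.168 |
| 30% | 490 | 0.650 | 0.179 |

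**Step 3: the planned contrast.** Take the baseline-to-6-month group × time contrast. Baseline is measured before randomisation, so under REML all 700 baselines per arm stay in the model. With m people per arm observed at 6 months, the variance per arm is

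(1 − ρ²)/m + (1 − ρ)²/700,

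and power ≈ Φ(0.15/√(2 × variance) − 1.960).

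For 20% loss (m = 560) and ρ = 0.5:

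- variance = 0.75/560 + 0.25/700 = 0.001339 + 0.000357 = 0.001696
- standard error of the group difference = √(2 × 0.001696) = 0.0582
- 0.15/0.0582 = 2.575, and Φ(2.575 − 1.960) ≈ 0.73

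Across correlations:

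| ρ | No loss | 20% loss |
|---|---|---|
| 0.4 | 0.73 | 0.66 |
| 0.5 | 0.80 | 0.73 |
| 0.6 | 0.88 | 0.82 |

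With no loss and ρ = 0.5 the change contrast has the same variance as the t-test, so 0.80 returns. Below 0.5 the planned contrast falls short of 0.80 even with complete data. At 0.6 it stays above 0.80 with 20% loss. Three-month values from people missing at 6 months are left out here; using them could add some information.

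**Step 4: a different analysis, for comparison only.** If the 6-month comparison were adjusted for baseline, power ≈ Φ(0.15/√(2(1 − ρ²)/m) − 1.960). With m = 560 and ρ = 0.5 this is Φ(2.898 − 1.960) ≈ 0.83. The Statistical Methods section specifies group × time and does not mention adjustment for baseline, so 0.83 does not describe the planned test.

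**The case against.** Nothing is miscalculated: 699 is right for the inputs given. Small losses hardly matter, since power is still 0.797 at 1% loss and 0.780 at 5%. A mixed model keeps partial data and may recover more than the t-test loses. The plan also reports effect sizes with 95% CIs at both follow-ups, so readers will see the precision achieved whatever the planned power was. All of this stands, and it limits the point to one about support for a stated figure.

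Two stronger readings are tempting, and the article supports neither.

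- **That any loss makes the 80% false, or that the trial is underpowered.** A reader might infer this from the margin of one person per arm. Step 3 shows that the planned contrast can exceed 0.80 even after 20% loss if the correlation is 0.6. Without that correlation, neither adequacy nor inadequacy can be shown.
- **That retention will be about 68%.** The Module 1 Exercise section mentions "a large 1-year follow-up online survey (n=2800, with a response rate of 68%) of full-time employees". That was a separate survey over one year, used to build a prediction model. The primary outcome here is measured at 3 and 6 months with reminders, and the article does not offer 68% as a forecast. Even at that rate (476 per arm), the Step 3 formula gives 0.60, 0.67, 0.76 and 0.86 for ρ of 0.4, 0.5, 0.6 and 0.7, which again falls on both sides of 0.80.

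The article format does not remove the point. The paragraph states a requirement and a power, and the Procedure section states the number randomised. Together they fit only near-complete follow-up, which other sections do not expect.

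**Conclusion.** The point holds as a lack of support for a stated figure. On the protocol's own t-test basis, 0.80 requires virtually complete outcome data; power is about 0.78, 0.76 and 0.71 at 5%, 10% and 20% loss. For the planned group × time contrast at 20% loss, power runs from about 0.66 to 0.82 as the correlation goes from 0.4 to 0.6.

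These sizes rest on assumed loss rates and correlations, equal SDs and a two-sided test, none of which the article states. The reproduction of 699 and the absence of a loss allowance need no assumption beyond two-sidedness, which the reproduced figure itself implies.

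**What to change.** Restate the Sample Size Calculation paragraph with four items: the assumed 6-month retention, the expected number per group with outcome data, the assumed baseline-to-6-month correlation, and the resulting power (or detectable d) for the group × time contrast named under Statistical Methods. Name the test and its sidedness.

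As an illustration with assumed inputs: with 20% loss (560 per group with 6-month data) and a correlation of 0.5, power for d = 0.15 is about 0.71 by two-sample t-test and about 0.73 for the group × time contrast under REML with all baselines retained. A baseline-adjusted figure of about 0.83 may be quoted only if the analysis itself is changed to adjust for baseline.

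The cost is the rewording of one paragraph. No extra enrolment is needed, and the design and analysis stay as they are. The downside is that the stated power may become less favourable.
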